## Abstract

**Background:**

Depression is a highly prevalent and disabling mental disorder with an incidence rate which appears to be increasing in the developed world. This fact seems to be at least partially related to lifestyle factors. Some hygienic-dietary measures have shown their efficacy as a coadjuvant of standard treatment. However, their effectiveness has not yet been proved enough in usual clinical practice.

**Methods:**

Multicenter, randomized, controlled, two arm-parallel, clinical trial involving 300 patients over 18 years old with a diagnosis of Major Depression. Major depression will be diagnosed by means of the Mini-International Neuropsychiatric Interview. The Beck Depression Inventory total score at the end of the study will constitute the main efficacy outcome. Quality of Life and Social and Health Care Services Consumption Scales will be also administered. Patients will be assessed at three different occasions: baseline, 6-month follow-up and 12-month follow-up.

**Discussion:**

We expect the patients in the active lifestyle recommendations group to experience a greater improvement in their depressive symptoms and quality of life with lower socio-sanitary costs.

**Trial registration:**

ISRCTN73931675

## Background

Depression is a highly prevalent mental disorder in our society, with 10 to 20% of the population experiencing a major depressive disorder/depressive episode during their lives [1-4]. From the health care system perspective, some studies confirm that 25-35% of patients consuming Primary Care services have a psychiatric condition, with over 80% of these patients presenting depression or anxiety disorders [5]. It is well known that General Practitioners (GPs) only refer approximately 5-10% of the psychiatric patients detected in Primary Care to Mental Health Services [6]. Despite this low referral rate, Mental Health Services in occidental countries are currently congested due to the high prevalence of minor psychiatric problems and this situation is very likely to worsen in the future [7]. Thus, it is of great interest to propose cost-effective alternatives for depression treatment in Primary Care settings which could improve efficacy to standard treatment while tolerability and security levels are sustained.

An essential issue regarding this alarming increment of the incidence and prevalence rates of depression is the fact that it seems to be occurring mainly in occidental countries [8,9]. Hence, it is necessary to rapidly clarify which variables could explain this trend in order to modify them [9,10]. It is presumed that lifestyle in occidental countries contribute to this increase in depression rates although specific factors involved have not been yet identified [8-10]. No important findings from the point of view of genetics or neurobiological factors have been published within the last decades, with the exception of a probable increase in alcohol and other drugs consumption which in any case is not sufficient to fully explain this trend [11]. Consequently, it has been more frequently attributed to environmental changes in our lifestyle especially those related to stress, nonconformity, competitiveness and loss of social relationships [12]. Besides the great importance of these described factors, in recent times other variables have been submitted which might possibly influence this increase [13]. In this sense, it has been suggested that occidental lifestyle implies changes in diet, hours of sleep, sun exposure and physical activity, all of which could play a role as a mediator variable for depression onset [8,9,12,13]. More and more people are decreasing their physical activity level and following a less healthy diet [14,15]. Moreover, there is a tendency towards a reduction of sleep hours and time of sunlight exposure [16,17]. It is well known that these changes impact the physiology of the brain which can lead to an increment in the vulnerability to depression [8]. Accordingly, it is not surprising that adjusting sleep hours, physical exercise, diet and sunlight exposure have been recommended separately by different research groups as a complementary or adjuvant treatment to pharmacotherapy and psychotherapy [18-20]. However, there is little investigation about the usefulness of GPs giving these simple hygienic-dietary measures as a recommendation jointly to antidepressant treatment in usual clinical practice conditions [9,12].

We conducted a preliminary study [9,13] where 80 patients undertaking standard treatment with antidepressants were randomly assigned to two groups. Patients in the intervention group received written recommendations about physical exercise, Mediterranean diet, sunlight exposure and sleep control. Obtained results were encouraging [9].

## Methods

### Hypothesis and objectives

The first hypothesis of the present study is that patients assigned to the intervention group receiving specific hygienic-dietary recommendations will show a significantly greater improvement in clinical measures of depression in comparison to control group patients. The second hypothesis is that significant differences in health costs will be found between both groups, with patients in the intervention group showing lower expenses. Therefore, the main objective is to evaluate the effectiveness and efficiency of giving specific hygienic-dietary recommendations to depressive patients in Primary Care settings. Secondary objectives are to evaluate changes in direct and indirect costs, to specify a profile of patients who benefit from this intervention and to identify the most frequent inconveniences for patients leading to non-adherence to these recommendations.

The present study is a randomized controlled clinical trial under “real world” conditions. Patients will be allocated to one of these two conditions:

1 Treatment as usual prescribed by their GP plus specified hygienic-dietary recommendations (intervention group)

2 Treatment as usual prescribed by GP plus unspecified hygienic-dietary recommendations (control group)

The study design is shown in Table 1.

**Table 1 T1:** STUDY SCHEDULE

	***“TRIAGE”***	***BASELINE***	***SIXTH MONTH***	***TWELFTH MONTH***
**Criteria compliance evaluation**	**X**			
**Discussion of the study information leaflet**	**X**			
**Signed Consent Form**	**X**			
**MINI Interview**		**X**		
**Sociodemographic questionnaire**		**X**		
**Clinic questionnaire**		**X**	**X**	**X**
**Physical parameters**				
**BP**		**X**		**X**
**HR**		**X**		**X**
**BMI**		**X**		**X**
**WAIST CIRCUMFERENCE**		**X**		**X**
**Blood Test**		**X**		**X**
**Scales**				
**BDI-21**		**X**	**X**	**X**
**STAI**		**X**	**X**	**X**
**EQ-5D**		**X**	**X**	**X**
**CSRI**		**X**	**X**	**X**
**Delivery of Hygienic-dietetic recommendations**		**X**		

### Study sample

Patients meeting the following inclusion criteria will be recruited: individuals aged 18 or older with a diagnosis of Major Depressive Disorder as stated by the DSM-IV, presenting mild to moderate depressive symptoms (as measured by BDI) of at least two months of duration, and having sufficient physical and cognitive aptitudes to understand and give written informed consent.

Among the exclusion criteria are the comorbidity with other medical conditions which would affect the Central Nervous System (CNS), other severe psychiatric disorders (except for anxiety disorders or personality disorders), or other non-controlled severe medical diseases, infectious or degenerative which would interfere with affective symptomatology or the adherence to the hygienic-dietary recommendations. Moreover, patients with delusions or hallucinations which are congruent or non-congruent with mood during study and patients with an important risk for suicide will also be excluded.

Recruitment of patients will take place in Primary Care Health Centers within the Balearic Islands, Catalonia and Aragon (Spain).

### Sample size and randomization

Statistical analysis will be based on head-to-head comparisons between the group receiving the hygienic-dietary recommendations and the “treatment as usual” group. Based on previous research, we expect that the mean difference between both groups in the main variable (BDI Total score) will be of at least 3 points (SD=6). Assuming an alpha risk of 0.01 and two tails, with a study power of 90% the corresponding sample size is 119 patients per group. With an estimated withdrawal rate of 20%, the sample size will require approximately 150 patients in each group. Thus, the total sample size of the study will be 300 patients.

Randomization will take place for each patient once participation is agreed to and the written informed consent signed. Every GP participating in this study will be provided with identically sealed envelopes codified with a numerical code that identifies the contents. These codes will be kept by the head of the research team. Half of the envelopes will contain the specific hygienic-dietary recommendations under consideration while the other half will contain “control” unspecified hygienic-dietary recommendations. In all cases, these recommendations will be written on a sheet of paper. The GP will randomly choose an envelope and ask the patient to follow the recommendations written inside.

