### Intervention

Patients in the intervention group will receive the following specific hygienic-dietary recommendations:

IN ORDER TO SPEED UP THE AMELIORATION OF YOUR DEPRESSIVE SYMPTOMS, WE ENCOURAGE YOU TO FOLLOW THESE HYGIENIC-DIETARY RECOMMENDATIONS:

1. Go to bed only when you feel sleepy and never before 11 p.m. Use your bedroom only for sleeping and sexual relations. Do not read, watch TV or stay inside the bedroom with any other purpose during the day. If you are unable to fall asleep within 15–20 minutes after going into bed, get up and get involved in an activity until you feel sleepy enough to go to bed again. Get up early, even if you have not slept properly. Do not get up later than 9 a.m. in any case. Do not lie down during the day and avoid taking a nap if you have not slept well the previous night.

2. Walk for a minimum of one hour every day, with a pace with which you do not feel breathless or are unable to speak. If you think you suffer any medical condition that would advise against this recommendation, please ask your doctor. Use comfortable trainers and wash after exercising by having a shower or a bath.

3. Expose yourself to environmental sun light, taking appropriated cautions to avoid sunburn or sunstroke (sunscreen, hat, etc.)

4. Try to follow a healthy and well-balanced diet. Eat at regular times, avoiding snacks between meals, especially sweets and sweetened drinks. Consume legumes and fish at least three times per week. Also, eat fruits, cereals, nuts and dried food, and other vegetables daily.

Patients in the control group will receive an identical envelope containing a sheet with the following unspecified hygienic-dietary recommendations:

IN ORDER TO SPEED UP THE AMELIORATION OF YOUR DEPRESSIVE SYMPTOMS, WE ENCOURAGE YOU TO FOLLOW THESE HYGIENIC-DIETARY RECOMMENDATIONS:

1. Sleep the hours that you feel your body needs.

2. Adapt the pace of daily physical activity to meet your needs best.

3. If exposed to sunlight take precautions to avoid sunburn or sunstroke (sunscreen, hat, etc.).

4. Try to eat a healthy and balanced diet.

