## Discussion

This study represents a great opportunity for the improvement with minimal costs of the effectiveness of depression treatment. Results of a preliminary study [9,13] pointed out that significant improvement of depressive symptoms can be achieved with this simple intervention. Its feasibility for the sanitary system derives from its low time consumption for health providers and the low cost of its implementation. Moreover, no significant adverse events or security problems derived from this intervention are expected.

Considering the low-restrictive nature of inclusion and exclusion criteria of the present study, problems for the recruitment of patients are not expected. The sample size will enable the determination of the profile of patients that could benefit from this simple intervention. It will also provide a better understanding of the reasons why some patients do not adhere to these recommendations, with the objective of eliminating this trend. The development of this research line in Primary Health Care settings is of great interest as well.

However, this study also has some limitations that will be taken into account. The main limitation derives from the fact that although GPs will be blinded to patient allocation, it is presumed that they will easily be able to identify which group the patient has been assigned to in the follow-up assessments. This is a potential bias as GPs could be induced to change pharmacological treatments based on this knowledge. In order to minimize this effect, we will ask participant GPs to stay as oblivious to patient allocation as possible. In case patient allocation is suspected, they will be asked to maintain a neutral attitude to patient comments regarding the recommendations they have received. Raters will also be blinded to treatment condition but, again, it will be easy for them to suspect patient allocation from the information provided by patients during the assessments. This could obviously introduce involuntary bias. To correct this possible bias, self-applied instruments will be preferred as main outcome variables.

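### The recruiting GP freely picks the envelope instead of following an independently generated sequence in fixed order, so allocation concealment is attempted but not adequately protected

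*Protocol article*

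**What the plan says.** The allocation procedure is in the protocol article, under Sample size and randomization, and has five stated elements:

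- **Timing.** "Randomization will take place for each patient once participation is agreed to and the written informed consent signed".
- **Supply.** "Every GP participating in this study will be provided with identically sealed envelopes codified with a numerical code that identifies the contents".
- **Key.** "These codes will be kept by the head of the research team".
- **Ratio.** "Half of the envelopes will contain the specific hygienic-dietary recommendations under consideration while the other half will contain" the control sheet. Whether the even split holds for each GP or only overall is not stated.
- **Act of assignment.** "The GP will randomly choose an envelope and ask the patient to follow the recommendations written inside".

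The Intervention section adds that the arms look alike from outside: "Patients in the control group will receive an identical envelope containing a sheet with the following unspecified hygienic-dietary recommendations". The Discussion section says that "although GPs will be blinded to patient allocation, it is presumed that they will easily be able to identify" the patient's group at follow-up.

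**The concern.** The GP who recruits the patient and prescribes the usual treatment also determines, by picking an envelope, which sheet the patient gets. A person's haphazard pick has no known allocation probabilities and leaves no trail. If a GP put an envelope back, opened a second one, or kept certain envelopes for certain patients, nothing in the described procedure would show it.

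At stake is protection against selection bias. A GP who thinks the specific sheet suits fitter or more motivated patients could, knowingly or not, let that belief shape who gets it. The self-rated outcome does not help, because it guards against biased rating and not against arms that differ from the start. Adjusting for baseline BDI would deal only with measured differences. The Discussion section considers imperfect blinding but not this risk.

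**Working it through.** **1. The plan's own figure.** The only arithmetic in this section is the sample size. Inputs: difference 3 points, SD 6, two-sided alpha 0.01, power 90%.

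- n per group = 2 × [6 × (2.5758 + 1.2816) / 3]² = 2 × 7.7148² = 119.04, against 119 stated.
- With 20% withdrawal: 119 / 0.8 = 148.75, so 149, against about 150 stated.

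The figure reproduces, and the allocation point changes nothing in it.

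**2. What each stated feature protects.**

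| Stated feature | Protects against | Leaves open |
|---|---|---|
| Sealed, identical envelopes | Telling the arms apart before opening | Opening one and taking another |
| Draw after signed consent | Withholding consent once the arm is known | Deciding whom to approach, and when, if the next arm is predictable |
| Code key held by the research team | Reading the arm from the code | Learning the code if codes repeat or follow a pattern (not stated either way) |
| Half the envelopes per arm | Gross imbalance, if the supply is used up | Predicting the next arm from what is left |
| GP picks any envelope | Nothing | Selecting, swapping or re-drawing |

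The last row is the defect. A rule to take the next envelope would contradict the sentence as written, because a GP following a sequence does not choose.

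**3. How predictable the supply could become.** Two assumptions are needed, and neither is in the document: each GP holds an equally split stack, and the GP learns every earlier allocation while still recruiting. With a and b envelopes left in the two arms, the best guess is the arm with more left. The expected number of correct guesses is

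G(a,b) = max(a,b)/(a+b) + [a/(a+b)] × G(a−1,b) + [b/(a+b)] × G(a,b−1), with G(0,0) = 0.

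For a stack of 4:

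- G(0,2) = 2
- G(1,1) = 0.5 + 1 = 1.5
- G(1,2) = 2/3 + (2/3) × 1.5 + (1/3) × 2 = 2.333
- G(2,2) = 0.5 + 2.333 = 2.833
- Share correct = 2.833 / 4 = 70.8%

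The same recursion for larger stacks gives:

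| Envelopes per GP | Correct guesses of next arm |
|---|---|
| 4 | 70.8% |
| 6 | 68.3% |
| 8 | 66.6% |
| 10 | 65.3% |
| 20 | 61.7% |

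Full concealment gives 50%. These are upper figures for this route, since a GP who knows only some past allocations would guess less well.

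**4. Size in BDI points.** This would need the share of allocations that are steered and the difference in prognosis between the patients steered each way. The document gives neither, so no bias figure is offered.

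**The case against.** The strongest reply is that a blind draw from identical sealed envelopes is a drawing of lots. It is harder to audit than a list, but it is not open choice of treatment. Much of this stands:

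- A reader might infer that allocation is not concealed at all, because the envelope carries a code tied to its contents. The document does not support this. The key is held away from the GP, and a number tells the GP nothing without it. The text does not say where the code is placed or whether codes repeat. Sequentially numbered envelopes would also map to arm through a list held elsewhere.
- Prediction and steering differ. Knowing that the remaining stack is lopsided shifts the odds of the next draw. It does not let a GP pull a chosen arm from identical sealed envelopes, though it can influence whom to enrol and when.
- Prediction needs knowledge gained during recruitment. The Discussion section places that knowledge at follow-up, and Table 1 puts the first follow-up at month 6. Recruitment length and stack size are not given. Earlier learning is possible, since the GP asks the patient to follow the sheet, but the text does not say whether the GP sees it.
- An article may leave opacity, shuffling and logging to the full protocol. Their absence is not the point here.

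What does not stand is the idea that the act of assignment is itself an omitted detail. The article states positively that the GP chooses. That removes any enforced order and leaves a swap or re-draw undetectable, whatever the key holder does.

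**Conclusion.** The point holds in this form: assignment is the recruiting GP's free pick, and concealment is attempted but not adequately protected. The possibility of undetected selection, swapping or re-drawing follows directly from the stated procedure. The predictability, 61.7% to 70.8% for stacks of 20 down to 4, depends on the two assumptions in the working and would be lower with partial knowledge.

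Two stronger readings should be resisted. One is that the trial loses its claim to be randomized. The procedure as intended is a draw of lots after consent, and the document shows a risk of selection bias, not its occurrence. The other is that the treatment effect is biased by some number of BDI points. Any such number would come from assumed inputs, and its size cannot be derived from the document.

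The correction belongs before enrolment, because no later analysis can reliably repair a compromised allocation.

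**What to change.** Replace the sentence on the GP's choice of envelope with a rule containing these elements:

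1. A computer-generated allocation list prepared by someone independent of recruitment, for example in permuted blocks of varying size within GP or centre. Sizes should vary and not be disclosed to GPs: a known fixed block of 4 would have the same 70.8% predictability as a stack of 4.
2. Opaque, sealed, sequentially numbered envelopes whose numbers carry no arm information.
3. The GP takes the lowest unused number and records the patient code and date on it before it is opened.
4. The research team reconciles used envelopes against the list.

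The cost is one protocol paragraph, preparation of the list and envelopes, and a little logging. No extra patients are needed.

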### Intervention

Patients in the intervention group will receive the following specific hygienic-dietary recommendations:

IN ORDER TO SPEED UP THE AMELIORATION OF YOUR DEPRESSIVE SYMPTOMS, WE ENCOURAGE YOU TO FOLLOW THESE HYGIENIC-DIETARY RECOMMENDATIONS:

1. Go to bed only when you feel sleepy and never before 11 p.m. Use your bedroom only for sleeping and sexual relations. Do not read, watch TV or stay inside the bedroom with any other purpose during the day. If you are unable to fall asleep within 15–20 minutes after going into bed, get up and get involved in an activity until you feel sleepy enough to go to bed again. Get up early, even if you have not slept properly. Do not get up later than 9 a.m. in any case. Do not lie down during the day and avoid taking a nap if you have not slept well the previous night.

2. Walk for a minimum of one hour every day, with a pace with which you do not feel breathless or are unable to speak. If you think you suffer any medical condition that would advise against this recommendation, please ask your doctor. Use comfortable trainers and wash after exercising by having a shower or a bath.

3. Expose yourself to environmental sun light, taking appropriated cautions to avoid sunburn or sunstroke (sunscreen, hat, etc.)

4. Try to follow a healthy and well-balanced diet. Eat at regular times, avoiding snacks between meals, especially sweets and sweetened drinks. Consume legumes and fish at least three times per week. Also, eat fruits, cereals, nuts and dried food, and other vegetables daily.

Patients in the control group will receive an identical envelope containing a sheet with the following unspecified hygienic-dietary recommendations:

IN ORDER TO SPEED UP THE AMELIORATION OF YOUR DEPRESSIVE SYMPTOMS, WE ENCOURAGE YOU TO FOLLOW THESE HYGIENIC-DIETARY RECOMMENDATIONS:

1. Sleep the hours that you feel your body needs.

2. Adapt the pace of daily physical activity to meet your needs best.

3. If exposed to sunlight take precautions to avoid sunburn or sunstroke (sunscreen, hat, etc.).

4. Try to eat a healthy and balanced diet.

### Outcomes and instruments

The main outcome in this study is symptom severity as measured by the validated Spanish version [21] of the Beck Depression Inventory (BDI-II) [22]. This is one of the most commonly used instruments to assess severity of depressive symptoms in pharmacological and psychological research. This instrument is widely used as it allows patient self-rating of depressive symptoms, avoiding evaluation bias. This is important to our study as, although they will be blinded to treatment condition, it is presumed that it will be easy for evaluators to identify which kind of recommendation each patient received during follow-up assessments. Moreover, the BDI is little influenced by somatic symptoms experienced by patients.

Other variables assessed in our study are:

– Socio-demographic variables such as gender, age, marital status, education level, occupation, economic status and hygienic-dietary habits.

– Psychiatric comorbidity will be assessed by means of the Mini International Neuropsychiatric Interview (MINI) and the State-Trait Anxiety Inventory (STAI). The MINI is a structured diagnostic psychiatric interview designed to diagnose according to DSM-IV and ICD-10 criteria [23,24]. This psychiatric interview will allow a diagnosis of Major Depressive Disorder at the baseline and also will permit the exclusion of other severe comorbid psychiatric disorders. The STAI is a self-rated inventory assessing two independent factors: State anxiety (a transitory emotional condition) and Trait anxiety (relatively stable anxious tendency). This inventory has been adapted and validated in the Spanish population [25].

– Quality of life will be measured with the EuroQol 5D (EQ-5D), which is a standardized instrument used as a measure of health outcome. The Spanish version will be administered [26].

– Health Care Services Consumption will be measured by the Spanish version of the Client Service Receipt Inventory (CSRI) [27], an instrument that allows the collection of data regarding social and sanitary services use as well as other data regarding economic impact (eg: time on sick leave) in the previous twelve months.

Assessments will take place at baseline and after 6 and 12 months.

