### Statistical analysis

In the analysis of clinical data, an ‘intention-to-treat’ analysis will be carried out. This analysis will include elemental ‘head-to-head’ descriptions and comparisons between intervention and control groups. Specifically, descriptive statistics (mean and 95% confidence intervals for metric variables with a normal distribution; median and interquartile range for metric variables without a normal distribution; frequency distribution for categorical variables) will be defined for each variable in both groups. To check the main hypothesis all variables will be compared (t0-tk) by means of the ANOVA test with adequate post-hoc contrasts for normally distributed variables or the Kruskal-Wallis H test. Finally, different multivariate analysis including multilevel regression analysis will be included if required. Improvement effect size will be calculated as well.

In the cost-analysis, direct costs will be calculated `ing to the medication-derived costs those derived from the use of sanitary services (visits to Primary Care, Specialized services and Emergencies, as well as hospitalizations). Medical cost will be calculated by determining price per milligram (including VAT) during the study period according to the 2011 Vademecum. Total cost of pharmacological treatment will be calculated multiplying price per milligram by daily dose in milligram and length of treatment (in days). Cost derived from health services and indirect costs will be calculated.

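### A twelve-month CSRI look-back at the month-6 visit reaches six months before randomization and overlaps both other reports, which dilutes any month-6 cost comparison

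*Protocol article*

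**What the plan says.** Under Outcomes and instruments, the Protocol article describes the CSRI as collecting use of social and health services together with "other data regarding economic impact (eg: time on sick leave) in the previous twelve months". This is the only recall period given for the instrument.

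The same section fixes the visits: "Assessments will take place at baseline and after 6 and 12 months". The Abstract agrees, and Table 1 marks the CSRI at all three visits.

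Time zero is close to the baseline visit. Allocation follows consent ("Randomization will take place for each patient once participation is agreed to and the written informed consent signed", Sample size and randomization), and Table 1 marks the row "Delivery of Hygienic-dietetic recommendations" at baseline only.

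The cost data serve the second hypothesis, that "significant differences in health costs will be found between both groups, with patients in the intervention group showing lower expenses" (Hypothesis and objectives). Efficiency is part of the main objective, and direct and indirect costs are a secondary objective. The Statistical analysis section lists the cost components. It does not say which CSRI report supplies them or how overlapping reports are handled.

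**The concern.** Visits six months apart, each looking back twelve months, must overlap, and the month-6 look-back must cross the point of randomization. Costs incurred before the recommendations were handed over then count as follow-up costs at month 6.

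The recall period is fixed when the patient is interviewed. If the form yields one total per item, no later analysis can divide the month-6 figure into its parts before and after randomization. What is at stake is the month-6 cost result, any change from baseline to month 6, and any total that combines the two follow-up reports. For a patient who withdraws between months 6 and 12, the only follow-up cost record would be the one that is half pre-randomization. The protocol expects 20% withdrawal overall but does not say how it is spread over time.

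**Working it through.** **Inputs.** Look-back of 12 months (Outcomes and instruments); visits at months 0, 6 and 12 (same section, Abstract, Table 1); randomization and delivery at about month 0 (Sample size and randomization, Table 1). The plan states no figure of its own to reproduce.

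**Windows.** A visit at month v covers months v - 12 to v.

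| Report | Window | Months before randomization | Months after |
|---|---|---|---|
| Baseline | -12 to 0 | 12 | 0 |
| Month 6 | -6 to +6 | 6 | 6 |
| Month 12 | 0 to +12 | 0 | 12 |

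**Overlap by half-year.**

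- A, months -12 to -6: baseline only
- B, months -6 to 0: baseline and month 6
- C, months 0 to 6: month 6 and month 12
- D, months 6 to 12: month 12 only

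**Contrast between groups at month 6.** Let the control group cost c per month throughout and the intervention group c - d per month after randomization.

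- The expected difference in the month-6 report is 6d, on a control total of 12c.
- As a proportion this is 6d/12c = 0.5 × d/c, half the saving that holds after randomization.
- The absolute difference of 6d is right for months 0 to 6, but it carries the noise of twelve months. If B and C each have standard deviation s and correlation ρ (assumptions; the article gives neither), the standard deviation of B + C is s√(2(1 + ρ)). Relative to C alone, the standardized difference is multiplied by 1/√(2(1 + ρ)): 0.71 at ρ = 0 and 0.50 at ρ = 1. Adjusting for baseline cost would recover part of this.

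**Change from baseline.** With monthly cost c0 before and c1 after randomization:

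- Month 6 minus baseline: (6c0 + 6c1) - 12c0 = 6(c1 - c0).
- Month 12 minus baseline: 12c1 - 12c0 = 12(c1 - c0).

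The shared half-year B cancels in the first line. The month-6 change is really C minus A, and under a constant effect it is half the month-12 change.

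**Can C be recovered from the totals?** The reports give A + B, B + C and C + D. A weighted sum equal to C alone needs weight 0 on A + B (to remove A), hence 0 on B + C (to remove B), and 0 on C + D (to remove D). That leaves nothing, so C cannot be separated.

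**If the two follow-up reports were added** (not stated in the article):

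- Recalled months: 12 + 12 = 24, of which 6 precede randomization, 6 + 6 are months 0 to 6 counted twice, and 6 are months 6 to 12.
- Saving: 6d + 12d = 18d against a true 12d, and 18/12 = 1.5.

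**Month 12 alone.** C + D covers months 0 to 12 once, with nothing before randomization.

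**The case against.** The case on the other side is substantial.

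- **The wording describes the instrument.** It sits in a list of scales and does not set the form for each visit. A shorter look-back at month 6 may stand in the full protocol or on the form. This stands as a limit on confidence, but nothing in the article points to it.
- **The phrase may attach only to economic-impact items.** On that reading no look-back is stated for service use, which drives direct costs. This also stands. The problem would then be confined to items such as sick leave, hence to indirect costs.
- **The second hypothesis can be tested cleanly.** The month-12 report covers the whole follow-up once, the baseline report covers the matching year before it, and no passage makes month 6 the time point for costs. A reader might infer that the cost hypothesis is compromised as a whole; the article does not support that.
- **Randomization balances the earlier months.** In expectation they are equal between groups, so they dilute the month-6 contrast and add noise. A reader might infer a spurious saving from this mixing; that does not follow.
- **Nothing says that the reports are summed.** A reader might take the 50% overstatement as a consequence of the plan. It follows only if someone adds the two reports. The cost paragraph neither says so nor rules it out.
- **The change from t0 is announced for clinical data.** The sentence "To check the main hypothesis all variables will be compared (t0-tk) by means of the ANOVA test" stands in the paragraph on clinical data and refers to the main hypothesis. Its reference to all variables could take in costs, but that is an inference.

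Medication cost is computed from price, dose and length of treatment, so it is affected only if that length is taken from the CSRI.

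**Conclusion.** The point holds in a limited form. As the article is written, 6 of the 12 months in the month-6 CSRI report precede randomization, and each half of that report is also recorded at another visit. A proportional month-6 saving is halved under a constant monthly effect, the month-6 contrast loses precision, and the baseline-to-month-6 change is half the month-12 change. The 50% overstatement is conditional on summing the follow-up reports.

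The conclusion assumes that the twelve-month look-back applies at every visit, that it covers at least the economic-impact items, and that the form yields totals rather than dated events. The halving also assumes a constant monthly effect. The month-12 cost comparison on its own is sound, and the BDI outcome and the sample size are unaffected. This should be fixed because costs carry a named hypothesis and the month-6 record cannot be repaired from its totals. Confidence is moderate.

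**What to change.** **Preferred.** At months 6 and 12, set the CSRI reference period to the six months since the last assessment, and sum the two reports for the twelve-month cost. The windows become 0 to 6 and 6 to 12, with no overlap and nothing before randomization. Use the baseline CSRI as a covariate and state its period, whether a matching six months or the existing twelve.

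**Alternative, if the twelve-month form is kept.** State that only the month-12 CSRI enters the cost comparison, with the baseline CSRI as covariate, and that the month-6 report is neither analysed as a follow-up cost nor added to month 12.

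**Cost.** The preferred change needs new wording on the form and one sentence in the analysis section, made before month-6 interviews begin. The cost history at baseline is shorter if that window is also cut to six months, and the twelve-month total then depends on two reports instead of one. The alternative needs only the sentence, but the month-6 CSRI then has no part in the cost comparison. If the month-6 form already uses a shorter period, stating that period and which reports make up the cost total is enough.
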